## Methods

### Ethics Approval

The study procedures described below have been approved by the institutional review boards of Sidra Medicine (2019-0004) and Northwestern University (STU00211149).

### Study Participants, Recruitment or Retention, and Informed Consent

A total of 210 women will be recruited. Women will be recruited from the prenatal care clinic at Sidra Medicine in Doha, Qatar. Women >18 years of age receiving prenatal care at Sidra Medicine—a women’s and children’s hospital—who are <28 weeks’ gestation at the time of study enrollment, are of Arab origin, and speak Arabic fluently will be eligible. Women meeting these criteria will be approached by Arabic-speaking research assistants while they are waiting for their prenatal health care appointment. Research assistants will administer the Edinburgh Postnatal Depression Scale (EPDS) [16] and the Generalized Anxiety Disorder-7 (GAD-7) item version [17]. To be eligible for the study, participants must score between 7 and 12 on the EPDS or 10-15 on the GAD-7, symptom ranges that are both indicative of mild to moderate symptoms of depression and anxiety, respectively. Participants who endorse a past history of major depression will also be eligible, while individuals endorsing current treatment for depression will be excluded given this study’s focus on the prevention of postpartum depression and anxiety. Other exclusion criteria have been minimized; however, women who self-reported receiving mental health treatment or having a serious mental health condition will also be excluded, as this may preclude women from regularly attending intervention sessions. Once eligibility is determined, the Arabic-speaking research assistant will introduce the study, answer any questions, and obtain signed informed consent from the participant.

Recruitment procedures emphasize the importance of participating in all MB sessions (for intervention participants) and remaining in the study through the 6-month follow-up assessment. The research team obtains ample tracking information at baseline, which includes the participant’s name, email address, home and cell phone numbers, and mailing address. The research team uploads contact information about each participant’s preferred mode of communication (eg, phone and text) at the time of recruitment.

### Randomization Procedures and Intervention Conditions

#### Randomization Procedures

Stratified permuted block randomization with blocks of sizes 2 and 4 will be used to randomize consenting women into the control arm or the intervention arm in a one-to-one fashion. The stratification will be based on the diabetic status of the woman. The randomization will be done by a statistician who is not involved in recruiting patients. A randomized list was created by the biostatistician, which was later uploaded to Research Electronic Data Capture (REDCap; Vanderbilt University) [18,19], a web-based software package for data management. This allows for the lack of human involvement on the part of the research team in the assignment of a participant to a group. It also allows for the on-the-spot assignment of participants into either the control or intervention groups.

#### Control Arm

Women randomized to the control arm will receive standard prenatal care delivered at Sidra Medicine.

#### Intervention Arm

Women randomized to the intervention arm will receive the culturally adapted MB intervention. MB consists of 12 sessions, each designed to last 15-20 minutes. The first 2 sessions provide (1) an understanding of the emotional and physical outcomes associated with stress, including concerns related to parent-child interaction, (2) strategies to notice one’s mood, and (3) an overview of how the remaining CBT content can help minimize stress levels. Sessions 3-5 focus on the CBT module of Pleasant Activities, while sessions 6-8 focus on Thoughts, and sessions 9-11 focus on Contact with Others. Session 12 is a course wrap-up and graduation. Intervention sessions provide concrete skills participants can use—for example, developing lists of pleasurable activities and strategizing how to overcome obstacles to engage in those activities. At the end of each session, a short personal project is provided to participants to encourage skill practice prior to the next session. Intervention sessions are delivered in-person, by phone, or via telehealth (Zoom and Microsoft Teams) by a mental health professional trained in MB. Sessions are intended to be delivered weekly or every other week, with flexibility given to deliver sessions at the same time to facilitate the timely completion of the intervention. Incentives will be provided to participants after completing each MB module to encourage their continued intervention participation. Additional content was added to selected sessions for the diabetic subgroup. This content was intended to draw links between the core MB cognitive-behavioral skills and diabetes management and self-care. For example, content that indicates how exercise and a healthy diet—aspects that are important for diabetes management—are also related to mental health, as both interventions have a positive effect on mental and emotional well-being, was added.

### Interventionist Training

Interventionist training in MB was provided by the senior author ([name]) and first author ([name]). Training was a 1-day in-person training conducted at Sidra Medicine. The first part of the training covered the conceptual underpinnings of MB (eg, its cognitive-behavioral framework), a brief history of previous implementation of MB, instruction on the format of the MB instructor manual, and discussion of implementation logistics. The second part of the training reviewed each of the 12 MB sessions from start to finish. Training was interactive, with opportunities for discussion and modeling the communication of material by the trainers. Training also involved group activities, where training attendees practiced delivering curriculum material and received feedback on strengths and areas needing improvement from the trainer and other training participants. We trained 30 individuals who met the following criteria: (1) employed as a nurse or health care professional or received graduate training in psychology; (2) were aged 18 years or older; and (3) had at least a bachelor’s degree in nursing or psychology, or equivalent mental health counseling training, experience, or certification. All trained individuals were fluent in Arabic.

### Data Collection Procedures and Study Assessments

The RCT includes 2 data collection time points—baseline and 6-month follow-up. We will attempt to collect 6-month assessments for intervention participants regardless of their engagement with the intervention. Participants will receive a remuneration of US $40 after completing each survey. Baseline and follow-up data will be collected and managed using REDCap. Women who do not choose to complete REDCap assessments will be contacted by phone by the research assistant to complete the assessment by phone or in person.

This study’s primary outcomes are a reduction in depressive symptoms, anxiety symptoms, and perceived stress. Secondary outcomes are closely linked with core MB content; secondary outcomes include behavioral activation, social support, mood regulation, decentering of thoughts, and MB skill use. The outcome associated with our exploratory aim is diabetes self-care. All measures have been validated in Arabic.

We will also assess various aspects of intervention implementation. We will conduct client surveys at the end of each MB module to assess clients’ perceptions of intervention acceptability and satisfaction. Each survey lasts 2-3 minutes and asks 3 questions pertaining to enjoyment with MB material, understanding of MB material, and anticipated use of MB material. Six months after a facilitator begins MB delivery with a client, the facilitator will receive a REDCap survey to report on the extent to which they covered all topics within an MB session (on average) and the extent to which clients were engaged in the MB material during intervention sessions.

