## Introduction

Perinatal mental health (PMH) disorders are common and have significant impacts on women, their infants, families, and communities [1,2]. Postpartum depression and postpartum anxiety are the 2 most common PMH disorders [3,4]. Systematic reviews have found a pooled prevalence of 15.5% across studies conducted in high-income countries [5], while systematic reviews of studies conducted in low- and middle-income countries found a higher pooled prevalence of 24.7% [6]. Among low- and middle-income countries, the highest prevalence rates were found in the Middle East and North Africa. Studies conducted in Qatar have found postpartum depression prevalence rates ranging from 18.6% to 27.3% [7,8].

An array of efficacious interventions exist that prevent postpartum depression [9,10], with several of these interventions demonstrating effectiveness in improving anxiety symptoms given the comorbidity with postpartum depression [11]. One intervention that has demonstrated efficacy in reducing depressive and anxiety symptoms and preventing the onset of new cases of postpartum depression is the Mothers and Babies (MB) course [12-15]. MB is a manualized intervention guided by a cognitive behavioral therapy (CBT) framework. CBT is characterized by a focus on (1) increasing pleasant activities, (2) focusing on one’s thoughts, and (3) the type and frequency of personal contacts (ie, social support). MB contains a module in each of these 3 areas. The content of MB is tailored to specific needs and issues related to pregnancy and the postpartum period.

Despite the prevalence rate of postpartum depression exceeding those found in Western countries and the availability of interventions effective in preventing postpartum depression, to date, there have been no intervention studies that have attempted to prevent postpartum depression among Arab women in the Middle East and North Africa region, including Qatar. The overarching goal of this study is to examine the feasibility, acceptability, and outcomes associated with MB delivered to women in Doha, Qatar. However, because MB was developed and previously examined when delivered to Western pregnant women, cultural adaptation was required before rigorous testing of the intervention in Qatar. The specific aims of this study are:

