### Pilot Study of Adapted MB

A byproduct of this project is deepening the capacity of mental health professionals in Qatar to address mental health with their perinatal clients. As such, 29 individuals fluent in Arabic were trained on the adapted MB manuals. The individuals included graduate students from the Doha Institute for Graduate Studies’ new master’s in psychology program, medical students from Weill Cornell Medicine in Qatar, PMH nurses from Hamad Medical Corporation and Primary Health Care Cooperation, and nurses from Sidra Medicine. The nomination of these trainees was performed based on their medical backgrounds, prior experience with CBT, and availability to deliver the intervention during the time frame of the research study. Training was led by the 2 multiple principal investigators ([name] and [name]). Training occurred over a full day and introduced trainees to the MB intervention’s core concepts and implementation considerations. Subsequently, each intervention session was reviewed with key considerations highlighted by the trainers. Emphasis was placed on highlighting places in the curriculum where adaptations were made to promote cultural and contextual fit. A second training was held for 14 of the individuals who completed the first training and indicated an interest in facilitating MB intervention sessions. This second training provided these 14 individuals with details on the study’s intervention and research procedures (eg, facilitator responsibilities, patient recruitment process). Training was delivered in both Arabic and English.

For the pilot study, 4 of these facilitators delivered the MB intervention to 10 pregnant individuals. The average number of sessions received was 7.0 (out of 12), and 4 individuals completed all 12 sessions. Baseline assessments were conducted to pilot procedures and measures to be used in the RCT. Client and facilitator feedback was used to modify study procedures and slightly adapt the intervention content.

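### Client acceptability is asked only at the end of each MB module, so women who stop before session 5 are never asked and the results over-represent women who stayed

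*Protocol article*

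**What the plan says.** The Introduction gives the overall goal as to "examine the feasibility, acceptability, and outcomes associated with MB delivered to women in Doha, Qatar", and acceptability is also in the title. Under Data Collection Procedures and Study Assessments, the client measure is set out as follows: "We will conduct client surveys at the end of each MB module", with the purpose of gauging how acceptable and satisfying clients find the course. Each survey "asks 3 questions pertaining to enjoyment with MB material, understanding of MB material, and anticipated use of MB material".

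The timing follows from the course structure. The Introduction lists three content areas and states that "MB contains a module in each of these 3 areas". The Intervention Arm section adds: "Sessions 3-5 focus on the CBT module of Pleasant Activities, while sessions 6-8 focus on Thoughts, and sessions 9-11 focus on Contact with Others". Sessions 1-2 are introductory and session 12 is a wrap-up. The same section ties payment to the same milestone: "Incentives will be provided to participants after completing each MB module".

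On uptake, the pilot section reports: "The average number of sessions received was 7.0 (out of 12), and 4 individuals completed all 12 sessions".

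Two other implementation measures are described: a facilitator survey six months after delivery starts, covering topic coverage and client engagement, and a count of sessions received. The 6-month participant assessment is attempted for intervention women whether or not they engaged, but no acceptability item is stated for it.

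**The concern.** The survey is triggered by reaching the end of a module. Staying in the course is itself a sign that a woman finds it acceptable, so the trigger selects on something close to what is being measured. A woman who leaves after one to four sessions is never asked. One who leaves after session 5 or 8 is asked once or twice, against three times for a completer.

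The other two measures do not fill the gap. The facilitator survey records the facilitator's view, and the session count shows that a woman stopped but not why. The imputation described under Statistical Analysis covers only the primary outcomes.

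At stake is how the acceptability result can be read. A favourable score among respondents could be taken as a finding about all women offered the adapted course, when it describes those who reached at least session 5, with most weight on those who finished.

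**Working it through.** **The plan's own figure.** The article gives no figure for acceptability. Its one sample-size statement reproduces: 105 × 0.80 = 84 analysed per arm, and with effect size 0.5 and two-sided alpha .017 the power is 0.803 (normal approximation) or 0.796 (noncentral t), against 80% stated. Nothing below depends on it.

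**Inputs.**
- Pilot: 10 women, mean 7.0 sessions, 4 completers of all 12 (Pilot Study of Adapted MB).
- Survey points: after sessions 5, 8 and 11 (Introduction and Intervention Arm).
- Intervention arm: 105 women (Power and Sample Size Calculations).
- Assumptions: sessions are received in order, and every survey that falls due is answered.

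**Sessions among non-completers.**
- Total: 10 × 7.0 = 70.
- From the 4 completers: 4 × 12 = 48.
- Left for the 6 non-completers: 70 − 48 = 22, a mean of 22/6 = 3.7, which is below session 5.

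**How many would be asked.** The mean does not fix the number, so all patterns of 22 sessions over 6 women, with at most 11 each, were enumerated.
- Most who can reach session 5: 4, since 4 × 5 = 20 ≤ 22 but 5 × 5 = 25 > 22. Never asked: 2 of 10.
- Fewest who can reach session 5: 0, since 6 × 4 = 24 ≥ 22 lets all six stop by session 4. Never asked: 6 of 10.

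**Who supplies the data.**
- Completers give 4 × 3 = 12 surveys.
- Non-completers give 0 to 6. The maximum has two women stopping after session 11 (2 × 11 = 22 sessions, three surveys each) and four receiving no session.
- Completers' share of surveys: 12/18 = 67% to 12/12 = 100%. If every woman had at least one session, non-completers give at most 4 surveys and the lower end is 12/16 = 75%.
- Completers' share of women with any survey: 4/8 = 50% to 4/4 = 100%.

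**Carried to the trial (assumption: pilot rates hold).**
- Unasked: 0.20 × 105 = 21 to 0.60 × 105 = 63 women.

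**Illustration of bias (assumed rates, not in the documents).** Take 90% acceptability in women who answer and 40% in those never asked. The survey reports 90%.
- With 20% unasked: 0.80 × 0.90 + 0.20 × 0.40 = 0.80.
- With 60% unasked: 0.40 × 0.90 + 0.60 × 0.40 = 0.60.
- The overstatement is 10 to 30 percentage points.

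**Sensitivity to the definition of a module.** If sessions 1-2 were also surveyed as a module, which is not how the Introduction counts them, 0 to 4 of 10 would never be asked. Completers would be 40-67% of respondents and would supply 64-73% of surveys.

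**The case against.** The strongest reply is that the design is better than a single end-of-course survey because it hears from partial completers. That stands. A reader might infer that everyone who stops early is silent, but a woman who stops after session 5 or 8 answers one or two surveys, and three if she stops after session 11. By head count, completers could be as few as half of respondents.

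Second, the direction of bias is not proven. A reader might conclude that satisfaction is overstated by construction. The article gives no reasons for stopping, and its Discussion names practical obstacles to attending appointments, such as illness, transport and childcare. Selection is plausible, but its size is unknown.

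Third, acceptability is not a headline trial result. The numbered aims assign it, with appropriateness and feasibility, to the pilot. The trial's aim is effectiveness on symptoms and stress. Acceptability is neither a primary nor a secondary outcome, and no single acceptability result or pooling rule is stated. This limits the weight of the point, although the title and overall goal still promise an answer.

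Fourth, pilot rates may not transfer: there were 10 women, and procedures and content were modified afterwards. This also stands.

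Fifth, the abstract mentions client and provider surveys both while the course is delivered and afterwards, and a condensed article may omit an exit survey held in the full protocol. That is possible. However, the only post-delivery implementation survey described in the methods goes to the facilitator. The point rests on the stated trigger for the client survey, not on a missing detail.

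**Conclusion.** The point holds in a limited form. As described, women who stop before session 5 give no acceptability data and later stoppers generally give fewer surveys, so the results lean towards women who stayed and are likely to be too favourable. On pilot figures, 20-60% of women would never be asked (about 21 to 63 of 105). A reader might take the upper end alone, but the pilot mean is equally consistent with the lower. The size rests on three things: the three-module reading, the transfer of rates from 10 women, and, for the 10 to 30 point illustration, assumed acceptability rates with no source in the article. This is a worthwhile improvement to an implementation measure and does not threaten the trial's primary comparison.

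**What to change.** Add to the 6-month assessment, for every woman randomised to MB:

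- Brief items on enjoyment, understanding and actual use of the material. The module survey's item on anticipated use should be reworded, because it does not mean the same thing once the course is over.
- One item on the reason for stopping. Women who attended no session should be asked only this item, since they cannot rate material they did not see.

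Report responses by number of sessions received, with all women randomised to MB as the denominator and non-response shown. Keep the module surveys as supportive data, since they are closer in time to the sessions. If the full protocol already contains a client survey for women who discontinue, say so in the methods and report it in the same way.

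The cost is about 2-3 minutes, judging by the stated length of the module survey, on an assessment that already has phone and in-person back-up. There are two downsides. Recall is longer. The expected 20% attrition (0.20 × 105 = 21 women) also means that some answers will still be missing, possibly more often among women who stopped. The change reduces the selection but does not remove it.

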### Safety and Data Monitoring

For any woman who endorses the suicidality question on the EPDS screener with a response that they think about suicide “quite often” or “sometimes,” the research assistant conducting the EPDS will escort the client to the outpatient mental health clinic, ensuring that the client is seen by a clinician. The clinicians in the Sidra Medicine outpatient clinic are trained to determine whether the client is in danger of harming herself or others and will determine the necessary steps to ensure the safety of the study participant. Regarding data monitoring, the study team will develop a series of data status and quality reports via an automated task, which study staff will review each week. These reports will focus primarily on reviewing missing data from collected assessments, accrual and retention, adverse events, and the number of women endorsing suicidal ideation.

### Statistical Analysis

A flowchart will be constructed based on the CONSORT (Consolidated Standards of Reporting Trials) guidance to show the number of recruited, excluded, lost to follow-up, and analyzed participants. Descriptive statistics will be used to summarize baseline characteristics overall and by study arm. As appropriate, mean (SD) and frequency (proportions) will be used to summarize continuous and categorical variables, respectively. Median (IQR) will be used in cases of skewed or nonnormal distributions. Analyses will use normal theory methodology as appropriate, and in cases of violations of assumptions, transformations or nonparametric analyses may be used. We will use SPSS (version 27; IBM Inc) to perform all analyses.

Analyses will be done using the intent-to-treat principle and will compare the 3 primary outcomes between study arms using the independent 2-tailed *t* test (or the Wilcoxon rank sum test in cases where outcomes were highly skewed). The analyses above will be repeated using univariate linear regression to be able to adjust later for any imbalances in baseline characteristics between the study arms and the baseline values of the primary outcomes. Additional analyses will include fitting multivariate linear regression models for each of the 3 main outcomes to assess the effectiveness of the intervention while adjusting for the baseline value of the outcome and any observed imbalances in participants between the 2 study arms. Unadjusted and adjusted mean differences in the primary outcomes between the 2 study arms will be presented along with their standard deviations and *P* values. For the primary outcomes, missing data at 6 months will be imputed using the average of the patients in that group or other methods such as multiple imputation by chained equations, and the primary analyses will be repeated as a sensitivity analysis. Secondary outcomes will be analyzed by comparing study arms using the chi-squared test (or Fisher exact test if expected cell counts are below 5) for categorical outcomes and the independent 2-tailed *t* test (or Wilcoxon rank sum test for highly skewed data) for numeric outcomes. Compliance with the intervention will be assessed by counting the number of intervention sessions received.

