**Methods:**

A multidisciplinary and multiethnic investigator team adapted MB to promote cultural and contextual fit for Arabic-speaking women. Intervention concepts were reviewed to ensure core content would be understood by Arabic-speaking women in Qatar. Subsequently, images, activities, and examples in the intervention manuals were adapted, as needed, to make the content more relevant to Arab culture. To deliver the adapted intervention, 30 Arabic-speaking individuals with mental health backgrounds were trained. The adapted intervention was subsequently pilot-tested with 10 pregnant women receiving prenatal care at Sidra Hospital in Doha. We are now conducting an RCT to examine the effectiveness of the adapted intervention. We plan to enroll 210 pregnant individuals who are Arabic-speaking, with 1:1 randomization to the MB intervention or usual prenatal care. Among the enrolled participants, a stratified subsample of 40 pregnant women with diabetes is being recruited. Data collection will take place at baseline and a 6-month follow-up. The primary outcomes are depressive and anxiety symptoms and perceived stress. Diabetes self-care is the exploratory outcome for the subsample of individuals with diabetes. Intervention implementation will be assessed via client and provider surveys during and after intervention delivery. Power and sample size were calculated using a 2-sided 5% effort rate and assumed analyses on the individual level, accounting for attrition of 20%.

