### Power and Sample Size Calculations

With 105 participants recruited per study arm and an estimated attrition of 20%, the study will be able to detect an effect size of 0.5 in any of the 3 primary outcomes using the independent 2-tailed *t* test with a power of 80% and a significance level of .017.

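### The unadjusted completer t test is ranked above the planned baseline-adjusted model, and the first-named imputation method, the group average, understates the standard error and cannot reveal dropout bias

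*Protocol article*

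**What the plan says.** All of this is in the protocol article.

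- **Primary comparison.** Statistical Analysis states: "Analyses will be done using the intent-to-treat principle and will compare the 3 primary outcomes between study arms". The test is an independent two-sample t test, with the Wilcoxon rank sum test for highly skewed outcomes.
- **Adjusted model.** The same section plans, as additional analyses, a linear regression for each of the three outcomes, adjusting for the baseline value and any observed imbalance. It promises both unadjusted and adjusted mean differences.
- **Missing data.** For the primary outcomes, "missing data at 6 months will be imputed using the average of the patients in that group or other methods", with multiple imputation by chained equations as an example of the other methods. With the imputed data, "the primary analyses will be repeated as a sensitivity analysis".
- **Power.** Power and Sample Size Calculations assumes 105 women per arm and "an estimated attrition of 20" percent, and states that "the study will be able to detect an effect size of 0.5 in any of the 3 primary outcomes". The calculation is for a two-sided t test at 80% power and alpha .017.
- **Follow-up.** Data Collection Procedures and Study Assessments plans a baseline and one 6-month assessment. The latter is sought from intervention women whatever their engagement, with phone or in-person completion as a fallback. The same section words the primary outcomes as reductions in symptoms and stress.

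**The concern.** A two-sample test cannot use a woman without a 6-month score, and there is only one follow-up. Since imputation belongs to the sensitivity analysis, the primary result is an observed-case comparison. This has two consequences.

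First, the unadjusted test makes no adjustment for the baseline score, which should be available for every randomised woman. If baseline symptoms influence who is lost, and do so differently in the two arms, the completers' baseline scores become unbalanced and the unadjusted difference carries that imbalance. Only one arm is offered a 12-session programme, so arm-specific loss is conceivable. The adjusted model that would deal with this is planned, but ranked second.

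Second, the sensitivity analysis should test how far the result depends on the missing women. Filling each gap with the arm's own mean cannot do that: it returns the same difference with a smaller standard error. The wording leaves the choice of method open, so this option could be the one used.

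**Working it through.** **Inputs from the protocol article:** 105 per arm, 20% attrition, effect 0.5 SD, two-sided alpha .017, power 80%. **Assumed, because the article gives no figure:** the baseline-to-6-month correlation r (0.3-0.6) and how dropout depends on baseline symptoms.

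**1. The plan's own figure.** Completers: 105 × 0.80 = 84 per arm, so 210 × 0.20 = 42 women are expected to lack a 6-month score. Power with 84 per arm at d = 0.5 and alpha .017 is 80.3% (normal approximation) or 79.6% (noncentral t). The stated 80% is reproduced and is the power of a test on completers. The sample size is not at fault.

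**2. Group-mean imputation with random dropout.** Adding 21 values equal to the arm mean of 84 leaves that mean, and so the difference between arms, unchanged. The sum of squares is also unchanged, but it is divided by 104 instead of 83, and n is taken as 105 instead of 84:

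SE ratio = √(83/104) × √(2/105) / √(2/84) = 0.799.

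The two-sided .017 critical value on 208 df is about 2.41. On the correct scale the test rejects at 2.41 × 0.799 ≈ 1.92, which on 166 df is a two-sided error of .056. Simulation with random dropout (6,000 trials) gave .055. With arm-specific dropout as in step 3, the error ranged from .064 to .127.

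**3. Completer t test under arm-specific dropout.** Simulation: no true effect, 20% loss in each arm, MB dropout odds multiplied by 2 or 3 per SD of baseline score, control dropout random, 6,000 trials per scenario. Negative values favour MB.

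| r | MB odds ratio | Raw score: bias (SD), error | Change score: bias (SD), error | Baseline-adjusted, same completers: bias (SD), error |
|---|---|---|---|---|
| 0.3 | 2 | -0.041, .021 | +0.090, .028 | -0.002, .014 |
| 0.3 | 3 | -0.056, .020 | +0.129, .044 | 0.000, .014 |
| 0.4 | 2 | -0.053, .023 | +0.076, .031 | -0.002, .018 |
| 0.4 | 3 | -0.075, .031 | +0.111, .044 | -0.001, .016 |
| 0.6 | 2 | -0.078, .030 | +0.050, .024 | -0.001, .017 |
| 0.6 | 3 | -0.109, .049 | +0.076, .034 | +0.002, .016 |

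The simulation standard error of an error rate near .017 is √(.017 × .983/6000) ≈ .0017, so the adjusted column is compatible with .017.

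**4. When there is no bias.** With dropout unrelated to symptoms (r = 0.5), the raw-score bias was 0.000 SD and the error .017. With the same dependence in both arms (odds ratio 2 or 3 in each, r = 0.5), the bias was 0.000 and -0.004 SD and the error .018 in both.

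**5. Power of the adjusted model on the same 84 per arm.** Adjustment divides the residual SD by 1/√(1 - r²), so the effective effect size is 0.5/√(1 - r²):

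- r = 0.3: 0.524, power 83.7%
- r = 0.4: 0.546, power 86.8%
- r = 0.5: 0.577, power 90.7%
- r = 0.6: 0.625, power 94.8%

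The unadjusted test has 79.6%.

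**The case against.** The strongest reply is that the plan already contains the remedy. Statistical Analysis specifies the baseline-adjusted regression for each primary outcome, promises both sets of mean differences, and names multiple imputation by chained equations. That stands: what remains at issue is the ranking of the analyses and the first-named imputation method.

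Two stronger readings are tempting, and the document does not support either.

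- **A reader might infer that the intent-to-treat label is false and that leaving out 42 women is what causes the bias.** The stated principle can fairly be read as analysis by allocated arm regardless of engagement, which fits the plan to follow intervention women whatever their attendance. The 42 is a planning figure, not an observed loss, and a CONSORT flowchart will show who was lost and analysed. In the scenarios above, adjustment removes the bias with the same women still missing, so including all 210 is not what corrects it there.
- **A reader might infer that the completer t test favours MB.** That needs raw 6-month scores and symptom-driven loss in the MB arm only. The outcomes are worded as reductions, and on change scores the same scenarios bias the result against MB. The article gives no dropout mechanism and no correlation. Entry by score range may narrow the baseline spread and lower r.

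Retention measures also help: US $40 per survey, phone or in-person completion, and weekly review of missing data. Stopping sessions is therefore not the same as missing follow-up. None of this rescues group-mean imputation, which is faulty even when dropout is random.

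**Conclusion.** The concern holds in limited form and is worth correcting.

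- **Firm, given the planned 20% attrition:** group-mean imputation repeats the completer difference with a standard error about 0.8 of its proper size. A nominal .017 test runs at about .05-.07 under random dropout or the same dropout dependence in both arms, and higher in most of the arm-specific scenarios.
- **Conditional:** the primary t test is open to bias of about 0.04-0.11 SD towards MB on raw scores, or 0.05-0.13 SD against MB on change scores, with type I error of about .02-.05. This rests on the assumed arm-specific dropout and r of 0.3-0.6. The bias is zero if dropout is unrelated to symptoms. The actual size and direction cannot be found from the document.
- **Gain from re-ranking:** adjustment on the same completers removes that bias and lifts power from about 80% to 84-95% (91% at r = 0.5).

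Neither adjustment nor multiple imputation corrects dropout driven by the unobserved outcomes themselves.

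**What to change.** 1. Name the linear model with arm, baseline score and diabetes stratum as the primary analysis of each of the three outcomes. The baseline-adjusted model is already planned; the stratum is added because randomisation is stratified by it.
2. Report the t test (or Wilcoxon) as supportive, described as an observed-case analysis by allocated arm.
3. Delete group-mean imputation. Specify multiple imputation by chained equations as the missing-data analysis of all 210 women, imputing separately by arm from baseline scores, diabetes stratum and, in the MB arm, sessions attended.
4. State that these analyses do not address dropout driven by unobserved outcomes. A sensitivity analysis for data missing not at random would be a useful addition.

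The change should be fixed before outcomes are compared by arm. It needs no new patients or data and no change to the sample size, only revised wording and a little more analysis work.
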